**Fig. 1 f0005:**
[figure not shown]
Design of the study and expected participants' flow.

### Instruments

2.7

Table 2 summarizes the instruments and time points of assessment that will be used.

**Table 2 t0010:** Variables, instruments and time points of assessment.

Dimension	Instrument	Abbreviation	Authors (German version)	Timepoints
*Primary outcome measure*				
Social anxiety symptoms	Social Phobia Scale & Social Interaction Anxiety Scale	SPS & SIAS	Stangier et al. (1999)	Pre, Mid, Post, FU

*Secondary outcome measures*				
Depressive symptoms	Patient Health Questionnaire	PHQ-9	Gräfe et al. (2004)	Pre, Mid, Post, FU
General anxiety symptoms	Generalized Anxiety Disorder Scale	GAD-7	Löwe et al. (2008)	Pre, Mid, Post, FU
Quality of life	SF-12 Health Survey	SF-12	Gandek et al. (1998)	Pre, Mid, Post, FU
Client satisfaction	Client Satisfaction Questionnaire	CSQ-8	Schmidt and Wittmann (2002)	Post
Negative effects	Negative Effects of the Treatment & Symptom Deterioration	INEP	Ladwig et al. (2014)	Mid, Post, FU
Diagnoses	MINI. Neuropsychiatric Interview	MINI 6.0.0	Sheehan et al. (1998)	Pre, Post, FU

*Hypothesized change mechanisms*				
Knowledge of SAD	Knowledge of SAD test	KSAD	Andersson et al. (2012)	Pre, Mid, Post, FU
Dysfunctional social cognitions	Social Cognitions Questionnaire	SCQ	Stangier et al. (1997)	Pre, Mid, Post, FU
Self-focused attention	Self-Consciousness Scale	SCS	Filipp and Freudenberg (1989)	Pre, Mid, Post, FU
Fear and avoidance	Liebowitz Social Anxiety scale	LSAS-SR	Stangier and Heidenreich (2004)	Pre, Mid, Post, FU
Safety behaviors	Social Behaviors Questionnaire	SBQ	Stangier et al. (1996)	Pre, Mid, Post, FU

Notes. Pre = baseline; Mid = mid-treatment (4 weeks after baseline); Post = post-treatment (8 weeks after baseline); FU = follow-up (6 months after baseline).

#### Primary outcome

2.7.1

SAD symptoms after eight weeks are the primary outcome of the study and will be assessed with the composite score of the Social Phobia Scale and the Social Interaction Anxiety Scale (SPS & SIAS; Mattick and Clarke, 1998; German version: Stangier et al., 1999). These two self-report questionnaires complement one another and are usually administered together. The SIAS assesses fears of social interaction (e.g., “I tense up if I meet an acquaintance in the street”), while the SPS focuses on fears of being judged by others (e.g., “I become anxious if I have to write in front of others.”). Both scales together consist of 40 items to be rated on a 5-point Likert scale (0 = “not at all” to 4 = “extremely”, ranging from 0 to 160 points, where high scores mean more general fear of social interaction). These two companion measures have been found to be valid, reliable and useful for clinical and research purposes. The German version of SIAS has an internal consistency of Cronbach's α = 0.94 (Stangier et al., 1999). The German version of the SPS also has an internal consistency of α = 0.94 (Stangier et al., 1999). They are both highly correlated with the other social anxiety measures, such as the Social Phobia and Anxiety Inventory and the Liebowitz Social Anxiety Scale (Hoyer and Margraf, 2003; Stangier et al., 1999). Stangier et al. (1999) calculated a cut-off value of 22 (for SPS) and 33 (for SIAS) as a discrimination criterion between German-speaking patients with social anxiety and different comparison groups. The composite score will be the simple average of the *z*-scores of SIAS and SPS, as recommended by Song et al. (2013) for continuous variables.

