**Methods:**

A total of 464 adults diagnosed with SAD will be randomized to one of 16 conditions containing combinations of the treatment components. The primary endpoint is SAD symptomatology at eight weeks. Secondary endpoints include symptoms of depression and anxiety, quality of life, and negative effects. Hypothesized change mechanisms are the increase of knowledge about SAD, the decrease of dysfunctional cognitions, the decrease of self-focused attention, and the decrease of avoidance and safety behaviors.

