### Sample size

2.8

The current study is powered for the first and primary research question, i.e., the main and interaction effects of the treatment components on the decrease of social anxiety symptoms. In the a priori power analysis, we assumed that the smallest clinically relevant difference would be a small effect size of Cohen's *d* = 0.2 for the main effect of an individual treatment component or interaction between components on pre-to-post change on social anxiety symptoms. Smaller effect sizes would be of little clinical interest and value. At an α level of 0.05, a statistical power (1-Beta) of 0.80, and a correlation between measurements with around 4- and 8-weeks interval of *r* = 0.50, based on our experience with clinical trials for SAD, we need a total of 384 participants (G*Power; Faul et al., 2007). Based on the finding that in 15 out of 17 studies, dropout rates (i.e., not providing assessment data at post-treatment) for ICBT for SAD were below 13% (Boettcher et al., 2013), we conservatively estimate a dropout rate of 20% for our study (*n* = 77 participants). Thus, we aim for a sample size of 464 participants, which results in 29 individuals per treatment condition.

As mentioned above, the logic behind how an experiment is powered differs between RCTs and factorial experiments. An RCT would compare the 16 conditions to each other, and power would be reflected in the per-condition sample size. If an RCT has a small per-condition sample size, such as 29 individuals per treatment condition, it does not have enough power to detect small effect sizes. By contrast, in factorial experiments, all participants receiving a specific component (e.g., cognitive restructuring, which is present in half of the conditions, i.e., in eight conditions) can be compared to participants who do not receive that component (also eight conditions, with 29 participants per condition). That yields a sample size of *n* = 232 per component (Collins, 2018). Since our study contains only components with two levels (absent vs present), the sample size to maintain the power to detect main effects and interactions is the same (Collins, 2018). For a detailed explanation of how factorial experiments maintain power to estimate main effects and interactions, see Collins (2018).

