### Statistical analyses

2.9

Reporting will follow CONSORT E-Health standards (Eysenbach and Consort-Ehealth Group, 2011). The primary outcome is the change in the composite score of SPS & SIAS from baseline to eight weeks (post-treatment). The analyses are carried out on the basis of the intention-to-treat approach (ITT; i.e., using all randomized participants). Our primary interest is in testing the main effects and interactions. For that, we will use linear mixed models repeated measures analysis of variance (ANOVA). This approach uses all available data on each subject and does not require the imputation of missing values but estimates parameters about missing values. Furthermore, mixed models account for the correlation between the repeated measurements. Main effects and interactions are calculated based on aggregates across experimental conditions. The levels of the factors will be represented numerically by −1 (absence of a component in a condition) and +1 (presence of a component in a condition), as recommended by Collins (2018). Significance testing of dichotomous data such as diagnostic status will be conducted with chi-square tests. Sensitivity analysis will be conducted to analyze the impact of dropouts on our results.

We will test mediation of the hypothesized change mechanisms (i.e., knowledge gain of SAD, decrease of dysfunctional social cognitions, decrease of self-focused attention, decrease of avoidance and safety behaviors) of the effect of the treatment components on primary and secondary outcomes (see Fig. 2 above). We will test mediation of the hypothesized change mechanisms by using an approach that allows multiple mediators in one model, as set out by Kraemer et al. (2002).

In addition, we will explore potential moderation of the treatment components by various measured variables (i.e., age, gender, country of origin, nationality, country of parents, mother tongue, relationship status, educational level, employment status, presence of comorbid disorder, use of medication, the severity of SAD). For the analysis of potential moderators, factorial ANOVA and multiple regression analysis will be used.

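### The primary outcome is worded as the week-8 symptom level in two places and as the baseline-to-week-8 change in two others; one baseline-adjusted week-8 contrast would settle it and gain power

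*Protocol article*

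**What the plan says.** Four places in the protocol article describe the primary outcome.

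- Abstract, Methods: "The primary endpoint is SAD symptomatology at eight weeks".
- Section 2.7.1, Primary outcome: "SAD symptoms after eight weeks are the primary outcome of the study and will be assessed with the composite score" of the SPS and SIAS.
- Section 2.8, Sample size: the effect to be detected is the "main effect of an individual treatment component or interaction between components on pre-to-post change on social anxiety symptoms".
- Section 2.9, Statistical analyses: "The primary outcome is the change in the composite score of SPS & SIAS from baseline to eight weeks".

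Section 1.1 also speaks of a decrease in social anxiety symptoms when it names the primary outcome.

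The planned analysis is a linear mixed model repeated-measures ANOVA on all randomized participants. The primary measure is taken at baseline, four weeks, eight weeks and six months (section 2.6, Table 2). The article does not say whether baseline enters as one of the repeated responses, as a covariate, or with its means held equal across component levels. Section 2.6 describes permuted-block randomization and mentions no stratification by severity.

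**The concern.** The abstract and section 2.7.1 read as a level at week 8; sections 2.8 and 2.9 read as a change. In a repeated-measures model with baseline among the responses, these are different coefficients. One is the present-minus-absent difference at week 8. The other is that difference minus the corresponding difference at baseline. They differ by whatever baseline imbalance chance leaves on that factor.

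The trial exists to say which of four components are active. If the deciding contrast is not fixed, a component could be declared active under one stated definition and not under the other, and either report could cite the protocol.

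**Working it through.** **The plan's own figure.** The 384 in section 2.8 can be reproduced as a condition-by-time interaction in a repeated-measures ANOVA. Take f = d/2 = 0.1, 16 groups, 4 measurements and r = 0.5, with noncentrality f² × N × 4/(1 − r) and 45 numerator degrees of freedom. The smallest N with power 0.80 is 372; the next multiple of 16 is 384 (power 0.818). The 16 groups and 4 measurements are inferred from the design; section 2.8 does not state them. The dropout step is 384 × 1.2 = 460.8, and the next multiple of 16 is 464. A condition-by-time test is a change-type test, which fits sections 2.8 and 2.9.

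**Inputs.** d = 0.2, α = 0.05, r = 0.50, N = 464 and 20% dropout are all from section 2.8. Week-8 data: 464 × 0.8 = 371.

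**Assumptions.** Two-sided test; unit SD at both visits; equal split on each component; week-8 data missing at random; all 464 have baseline; the four-week and six-month values are left out.

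**Variances** of the present-minus-absent contrasts, with baseline as a repeated response:

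- Baseline difference: 4/464, so SE = 0.093.
- Level at week 8: 4 × [(1 − r²)/371 + r²/464] = 4 × [0.75/371 + 0.25/464] = 0.01024, so SE = 0.101.
- Change: 0.01024 + 4/464 − 2 × 4r/464. At r = 0.5 the last two terms cancel, so SE = 0.101 again.
- Correlation of the two estimates: (0.01024 − 4 × 0.5/464)/0.01024 = 0.58.

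**Results at r = 0.50.**

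- Power of either test at d = 0.2: z = 0.2/0.1012 = 1.98, giving about 51%.
- From the bivariate normal with correlation 0.58, at least one test is significant in 65.8%. Exactly one is significant in 2 × 65.8% − 50.7% − 50.7% = 30%.
- With no true effect, at least one is significant in 8.8%, against 5% for a single fixed test.
- The two estimates differ by more than 0.1 SD (half the target effect) in 28% of effects. For at least one of four components this is 1 − 0.72⁴ = 73%.

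**With baseline adjusted for.** The contrast has variance 4(1 − r²)/371 = 4 × 0.75/371, so SE = 0.090, z = 0.2/0.090 = 2.22 and power is about 60%. Using the week-8 score or the change as the response gives the same component estimate.

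**Other correlations** (assumed values, same formulas, d = 0.2 in units of the score's SD):

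| r | Power, level | Power, change | Exactly one significant | Power, baseline-adjusted |
|---|---|---|---|---|
| 0.3 | 49% | 39% | 28% | 52% |
| 0.5 | 51% | 51% | 30% | 60% |
| 0.7 | 53% | 71% | 36% | 77% |
| 0.8 | 54% | 87% | 40% | 89% |

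The adjusted contrast has the highest power in every row.

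**The case against.** The best reply is that this is layered wording, not a conflict. The abstract and section 2.7.1 name the construct, instrument and time point; the analysis section supplies the metric, and that metric is change. Sections 1.1 and 2.8 point the same way, and 384 reproduces as a change-type test. The article nowhere plans an unadjusted week-8 comparison as the primary test. The handling of baseline is commonly left to an analysis plan.

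Much of this stands. A reader might infer that nothing in the article indicates which definition governs. That goes too far: the weight of the text is on change. A reader might also infer that the trial will run at an inflated error rate. That does not follow either, because 8.8% arises only if someone chooses between the readings after seeing the data.

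What remains is that section 2.7.1, the section that defines the primary outcome, and section 2.9 each say outright what that outcome is, and they say different things. A likely intention does not align them, and the named model produces both coefficients.

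**Conclusion.** The point holds as an inconsistency in the definition of the primary outcome, with change the probable intention. Under randomization both readings have the same expected value, so there is no bias, and at the plan's r = 0.50 the choice between them does not alter power. The open question is which test decides. On the assumptions above, the two tests split in about 30% of cases at d = 0.2, and a choice made after seeing the data would carry about 8.8% false positives per effect.

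The 51% should not be read as a result of the inconsistency. It is the power of a single two-sided component contrast at d = 0.2 with these numbers, under either reading. How it relates to the planned 80% is a separate question about section 2.8.

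Aligning the wording alone would be close to clerical. The practical gain comes from also fixing the baseline adjustment, which removes the ambiguity and raises power from about 51% to about 60% at r = 0.50.

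**What to change.** State one primary outcome in the same words in the abstract and in sections 2.7.1, 2.8 and 2.9. Name the primary test as the component contrast (main effect or interaction) on the SPS and SIAS composite at week 8, adjusted for baseline. Baseline can enter as a covariate or as a repeated response with its means constrained equal across components. The model term that decides each primary test should be named.

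This costs a few sentences, settled before outcome data are analysed. Baseline is already collected from every participant, so no new data or participants are needed. If the trialists prefer unadjusted change, aligning the abstract and section 2.7.1 with section 2.9 would remove the inconsistency but not bring the gain in power.

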#### Secondary outcomes

2.7.2

##### M.I.N.I. International Neuropsychiatric Interview for DSM-IV 6.0.0 (M.I.N.I.; Sheehan et al., 1998; German version: Ackenheil et al., 1999)

2.7.2.1

M.I.N.I. is a brief structured diagnostic interview for assessing psychiatric diagnosis based on the DSM-IV. The specificity of the M.I.N.I was reported as suitable for all diagnoses (ranging from 0.72 to 0.97; 0.81 for SAD; Sheehan et al., 1997). In our study, the M.I.N.I. interview will be administered via telephone. It will assess depressive episodes, suicidality, manic and hypomanic episodes, panic disorder, agoraphobia, SAD, obsessive-compulsive disorder, post-traumatic stress disorder, substance abuse and addiction, psychosis, anorexia and bulimia nervosa and generalized anxiety disorder. The diagnosis of SAD will serve as an eligibility criterion and a secondary outcome measure (an absence of diagnosis at post-treatment and follow-up suggesting treatment success).

##### Patient Health Questionnaire (PHQ-9; Spitzer et al., 1999; German version: Gräfe et al., 2004)

2.7.2.2

Symptoms of depression will be measured with the PHQ-9. This widely used self-report measure consists of nine questions assessing characteristic symptoms of major depression described in DSM-V distributed in nine items on a 4-point Likert scale. Higher scores indicate more severe depression. The German version of the PHQ-9 has also shown good internal consistency (Cronbach's α  = 0.88; Gräfe et al., 2004; Kroenke et al., 2010; Löwe et al., 2004).

##### Generalized Anxiety Disorder Scale (GAD-7; Spitzer et al., 2006; German version: Löwe et al., 2008)

2.7.2.3

The GAD-7 measures seven general anxiety symptoms (i.e., feeling nervous, worrying, having trouble relaxing, restlessness, feeling annoyed or irritable, and feeling afraid that something awful might happen). Higher scores indicate more severe general anxiety symptoms. The internal consistency of the GAD-7 is good in both the original and German versions (Löwe et al., 2008; Spitzer et al., 2006).

##### Short-Form Health Survey-12 (SF-12; Ware et al., 1996; German version: Gandek et al., 1998)

2.7.2.4

Quality of life is assessed with the SF-12. Its two subscales measure the physical and mental aspects of health-related quality of life. The SF-12 shows good psychometric properties (e.g., internal consistency of α = 0.83) and is equivalent to the long-form, the SF-36 (Gandek et al., 1998; Ware et al., 1996).

##### Client Satisfaction Questionnaire (CSQ-8; Attkisson and Zwick, 1982; German version: Schmidt and Wittmann, 2002)

2.7.2.5

The CSQ-8 is a self-report questionnaire that assesses the general level of satisfaction with the service received. It was developed to measure satisfaction with inpatient treatment. The original version shows good internal consistency (Cronbach's α = 0.91; Attkisson and Zwick, 1982). In this study, we will use a version that was adapted for internet-based treatments.

##### Negative Effects of the Treatment (INEP; Ladwig et al., 2014)

2.7.2.6

The INEP assesses any adverse effects on social, intrapersonal or work-related situations and whether they are attributed to the intervention. As in other studies, the INEP will be slightly adapted for use within internet-based interventions. The original scale was developed and validated in German and showed good internal consistency (Cronbach's α = 0.86; Ladwig et al., 2014).

##### Adherence

2.7.2.7

Following the suggestion of Donkin et al. (2011), a composite score to measure adherence and dosage will be created by averaging the *z*-scores of several variables: time spent in the intervention, the number of modules completed, the number of exercises completed, and the number of clicks in the intervention.

In addition, socio-demographic variables such as age, gender, country of origin, parent's country of origin, mother tongue, relationship status, educational level and employment status are assessed.

#### Assessment of hypothesized mechanisms of change

2.7.3

The secondary aim of this study is to better understand which mechanisms of change mediate the relationship between treatment components and symptom reduction. For this, we will also assess variables hypothesized to mediate change for every treatment component. Fig. 2 shows a conceptual model of the expected effects of the four treatment components on the hypothesized change mechanisms and primary and secondary outcomes.

**Fig. 2 f0010:**
[figure not shown]
Simplified conceptual model of the effects of the four treatment components on the hypothesized change mechanisms and primary and secondary outcomes.

##### Knowledge of SAD test (KSAD; Andersson et al., 2012; Berg et al., 2020a)

2.7.3.1

The KSAD assesses basic knowledge around the condition of SAD and its treatment. It includes 11 questions, each with one correct answer (out of three possible choices). In addition, each response is rated in terms of how confident the participant is about the response with three response options (Guessing, Pretty Certain, Confident). A higher score indicates more knowledge. Questions cover the content of the psychoeducation component of the Shyne program (e.g., the definition of SAD, general principles of CBT, safety behaviors, avoidance, negative automatic thoughts, attentional shift, exposure). Scores of knowledge of SAD are calculated in two ways: (a) a total score based on the total number of correct answers and (b) a weighted total score in which certainty of answers was factored in. Reliability analyses showed a low Cronbach's alpha of α  =  0.40 for the raw scores, a high Cronbach's alpha of α  =  0.86 for the certainty ratings, and an alpha of α  =  0.56 for the weighted scores (Andersson et al., 2012).

##### Social cognitions questionnaire (SCQ; Wells et al., 1993; German version: Stangier et al., 1996b)

2.7.3.2

The SCQ is a self-rating scale that assesses typical negative social cognitions of socially anxious individuals. It is composed of 22 items, ranging from 22 to 110, grouped in three subscales (“negative self”, “performance anxiety”, and “fear of showing bodily symptoms”). Higher scores mean more negative social cognitions. The Cronbach's α for the whole German version scale is α = 0.89.

##### Self-Consciousness Scale (SCS; Fenigstein et al., 1975; German version: Filipp and Freudenberg, 1989)

2.7.3.3

The SCS measures self-focused attention (or self-consciousness) in two dimensions: private self-consciousness and public self-consciousness. The German version consists of 27 items, which are rated from 1 (“very rarely”) to 5 (“very often”). Higher scores indicate more self-focused attention. Both subscales have shown good internal consistency (Cronbach's α = 0.87 and α = 0.86, respectively; Hinz et al., 2010).

##### Liebowitz Social Anxiety Scale, self-report (LSAS-SR; Baker et al., 2002; German version: Stangier and Heidenreich, 2004)

2.7.3.4

The LSAS-SR measures SAD symptoms. It comprises 24 items, divided into two subscales (anxiety and avoidance, 12 items each) scored on a Likert-type scale of four points and is rated in terms of frequency (never, occasionally, often and usually). In this study, and as a measure of a hypothesized mechanism of the change, only the avoidance subscale will be used. LSAS-SR shows good internal consistency (α = 0.96 for the total scale and α = 0.92 for the avoidance scale).

##### Social Behaviors Questionnaire (SBQ; Clark et al., 1995; German version: Stangier et al., 1996a)

2.7.3.5

The SBQ assesses the use of safety behaviors in social situations with 27 items. The frequency of each behavior is rated on a 4-point scale (from 0 = never to 3 = always). “Avoid eye contact”, “try to control shaking”, “rehearse sentences in your mind” are examples of safety behavior assessed by the SBQ. The items on the SBQ are a mixture of discrete behaviors (e.g., hide your face, grip glasses tightly) and broad strategies (e.g., make an effort to come across well, try not to attract attention). Studies with adult populations revealed acceptable internal consistencies (Cronbach's α = 0.69).

